### Randomization and masking

#### Randomization

The block randomization method will be used. The appropriate segment length will be selected and SAS9.4 (SAS Institute Inc., Cary, NC, USA) used to generate a randomization sequence for 100 subjects (test group, control group) according to a 1:1 ratio and list the treatment allocation corresponding to serial numbers 001–100 (that is, a random coding table). The placebo is made of SHGBZK Chinese medicine (5%) and dextrin (95%) to ensure it mimics the appearance, smell, and taste of SHGBZK. Both researchers and participants will not know the assignment. The randomization sequence table will be kept in a file. The method, process, group setting, and grouping result of the randomization sequence will be recorded so it can be checked when necessary. Information on intervention assignments will be kept in the third consulting center of biomedical statistics.

#### Blinding

Design: In this study, two stage blinding is used. The first stage blinding is represented by groups A and B. The second stage blinding is represented by the corresponding test drug and placebo.

Blinding management and preservation: Blinding is carried out by the statistical unit. The clinical trial unit and the statistical analysis unit are deposited in accordance with the relevant regulations after the blinding is sealed. The process of drug coding will be written by the blinder and saved.

Emergency unblinding: If an adverse event occurs during the study, the main investigator can decide whether to unblind according to the subject. The investigator needs to record the time, location, and cause of the unblinding in the medical record and Case Report Form (CRF) (the group information after unblinding should not be recorded in the CRF).

### Intervention measures

The two groups will receive basic treatment for COPD according to the 2017 GOLD Guidelines for Chronic Obstructive Pulmonary Disease. Patients will stick to the treatment they used to take as much as possible and will be given the trial treatment when AECOPD occurs during the study. Patients in the experimental group will take SHGBZK, while the control group will take SHGBZK placebo. The TCM granules are compound preparations of Chinese herbs; its main components are shown in Table 1 . Each bag of SHGBZK granules (batch number 180606) contains 3 g. The components of the TCM granules are produced and packed by An Hui Ji Ren Pharmaceutical Co. Ltd according to Good Manufacturing Practice (approval number AH20160363), Anhui, PR China. The test results of drug quality were consistent with the required quality standards. Each type of granule will be given orally, four bags each time, three times a day for 24 weeks.

**Table 1 Tab1:** Main components of the traditional Chinese medicine treatment

Chinese name	Latin name	Amount (g)
Chinese herbal formula San-Huang Gu-Ben Zhi-Ke		
Huang Qi	*Astragalus propinquus*	15
Huang Jing	*Polygonatum sibiricum*	12
Chen Pi	*Pericarpium citri reticulatae*	10
Bai Bu	*Stemona japonica*	10
Wu Wei Zi	*Schisandra chinensis*	8
Chi Shao	*Paeonia lactiflora* Pall	10
Huang Qin	*Scutellaria baicalensis* Georgi	8

Patients need to take the medication as directed by the doctor. The use of glucocorticoids, antibiotics, mucolytic agents, and antitussive agents is prohibited during the study except if AECOPD occurs, and oral or external Chinese medicine preparations with the effect of tonifying the spleen and lung are prohibited during the trial period. Patients will be given a daily diary to record their trial medication compliance as well as use of any other therapies and occurrence of adverse events. Patients will be asked to return their medication bags monthly during the treatment period to enable the counting of left-over capsules as well as part of participant adherence monitoring.

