**Methods/design:**

This study is a randomized, double-blind, placebo-controlled trial. A total of 100 patients with stable COPD diagnosed with deficiency of lung qi and spleen qi will be recruited and randomly assigned to one of two treatment groups: SHGBZK treatment, *N* = 50; placebo treatment, N = 50. The two groups will receive basic treatment for COPD according to the 2017 GOLD Guidelines for Chronic Obstructive Pulmonary Disease. Patients will stick to the treatment they used to take as much as possible, and will be given present general treatment when acute exacerbation of COPD occurs during the study. Both groups will receive a 24-week intervention and patient status will be assessed at 24 weeks and then 28 weeks after treatment. After the 24-week treatment, patients will be followed up for another 28 weeks. Outcome measures, including the frequency and duration of acute exacerbation, lung function, traditional Chinese medicine symptom score, exercise capacity, and quality of life will be assessed.

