## Background

Chronic obstructive pulmonary disease (COPD) is characterized by persistent and limited airflow, which can be progressively aggravated. The repeated acute exacerbation of COPD (AECOPD) can lead to a variety of complications that lead to the disease worsening [1]. Reducing AECOPD is a major goal of COPD management and an important indicator for evaluating treatments. According to statistics [2], the global incidence of COPD is about 10% of the population. It is expected that COPD will have the third highest fatality rate in the world [3] and its economic burden will rank fifth in the world by 2020. In China, the prevalence of COPD in people over 40 years old is 8.2% [4], the number of deaths due to COPD exceeds one million each year, and the number of disabled people over five million. In addition to pulmonary symptoms, studies have shown that the most common complications of COPD patients are cardiovascular disease, diabetes, asthma, and anemia [5]. Most patients have one or two complications, which increase the social and economic burden. And most patients have mental anxiety symptoms [6], which seriously affect their working ability and quality of life [7]. As COPD can be prevented, effective preventive measures will help to delay the recurrence and progressive aggravation of the disease.

Current treatments for COPD include inhaled corticosteroids and bronchodilators [8]. Although effective at alleviating symptoms, these treatment methods do not alter disease progression. There is a pressing need to find better treatments [9] for improving clinical symptoms, lowering lung function decline, reducing mortality, and shortening hospitalization time. Traditional Chinese medicine (TCM) has a great advantage in reducing the risk for severe exacerbation, improving lung function, positively impacting quality of life, and improving exercise capacity in stabilized patients with COPD, which can supplement the deficiency of modern medical treatment [10].

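### The glucocorticoid ban states no route and conflicts with continuing guideline and prior treatment, and two different rules are given for treating an AECOPD

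*Protocol article*

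**What the plan says.** The Intervention measures section sets three rules on background drugs:

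- Guideline care: "The two groups will receive basic treatment for COPD according to the 2017 GOLD Guidelines for Chronic Obstructive Pulmonary Disease".
- Prior care: "Patients will stick to the treatment they used to take as much as possible".
- A ban: "The use of glucocorticoids, antibiotics, mucolytic agents, and antitussive agents is prohibited during the study except if AECOPD occurs".

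The Fig. 1 caption repeats all three. Two other places bear on the ban. The Background states: "Current treatments for COPD include inhaled corticosteroids and bronchodilators". The Exclusion criteria rule out frequent users of oral glucocorticosteroids and say nothing of inhaled ones.

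On exacerbations, the Intervention measures section and the Fig. 1 caption say patients "will be given the trial treatment when AECOPD occurs during the study". The Abstract (Methods/design) has almost the same sentence but says they "will be given present general treatment when acute exacerbation of COPD occurs during the study". The study product follows a fixed schedule: "Each type of granule will be given orally, four bags each time, three times a day for 24 weeks".

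**The concern.** There are two separate problems.

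First, a patient who enters on an inhaled corticosteroid is told to continue prior treatment as far as possible and is also told that glucocorticoids are prohibited outside an exacerbation. One investigator may stop the drug and another continue it, and each can point to a sentence in support.

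Second, a reader cannot tell from the operative section what a patient receives when an exacerbation occurs. Taken literally, it is the product the patient is already assigned to take every day.

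Both bear on the primary outcome, AECOPD frequency. Patients are selected for high risk (at least two exacerbations, or one hospitalization for exacerbation, in the past year), so whether maintenance drugs continue is also a safety matter. The meaning of the result is at stake too. The Sample size section cites 1.17 per year under conventional medicine and 0.68 per year under conventional medicine plus TCM, which points to an add-on comparison. Whether the trial delivers that comparison depends on which background rule sites follow.

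**Working it through.** No figure in the plan depends on this point, so the check sets the texts side by side.

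**Background drugs**

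1. *Is the ban limited by route?* No. It names glucocorticoids as a class in both the Intervention measures section and the Fig. 1 caption. The Exclusion criteria, by contrast, specify oral use, so the authors do state a route in one place and not in the other.
2. *Does the document place a glucocorticoid among ordinary COPD treatments?* Yes. The Background names inhaled corticosteroids alongside bronchodilators.
3. *Can an inhaled-steroid user enter?* Yes. No inclusion or exclusion criterion bars inhaled use.
4. *What is that patient then told?* To keep prior treatment as far as possible (rule 2), and not to use a glucocorticoid outside an AECOPD (rule 3). Nothing says which rule prevails.
5. *Does the same hold for the other banned classes?* Only more weakly. Nowhere does the document place mucolytics or antitussives in guideline basic treatment. For them the tension rests on the prior-treatment sentence alone.

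**Treatment at an exacerbation**

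| Place | What is given at an AECOPD |
|---|---|
| Abstract, Methods/design | Present general treatment |
| Intervention measures | The trial treatment |
| Fig. 1 caption | The trial treatment |

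6. *Does the trial-treatment wording fit the schedule?* No. The granules are taken daily for 24 weeks whether or not an exacerbation occurs.
7. *Does it fit the follow-up?* No. The Abstract gives 24 weeks of treatment and a further 28 weeks of follow-up: 24 + 28 = 52 weeks, which agrees with the last visit at week 52. The Primary outcome measure section counts exacerbations in both periods. So 28/52 = 54% of the counting period falls after the product has ended.

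**Link to the primary outcome**

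8. The Primary outcome measure section describes an AECOPD as symptoms beyond usual daily variation that call for an alteration of regular drugs, and adds a count of major and minor symptoms. If regular medication is ambiguous, so is that part of the definition. For example, restarting a maintenance drug that was stopped at entry because of the ban could be read as a change in medication or as a return to the usual regimen.
9. The ban is lifted only by an AECOPD. Labelling an episode as an exacerbation is therefore the route to the prohibited drugs, which ties the ban to event recording.
10. Differences between sites are possible. The Quality of life section refers to an investigator in each center, and the Statistical analysis section refers to center effects.

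**The case against.** The best defence is that ordinary reading resolves most of this. The prior-treatment sentence is qualified, so it can be taken to mean that usual drugs continue apart from those listed. The ban sits beside antibiotics and has an exacerbation exception, so systemic glucocorticoids may be all that was meant. Because the ban lifts at an AECOPD, the banned classes become available then, which agrees with the Abstract and makes the trial-treatment wording look like a slip. Randomization and blinding mean that any ambiguity falls on both arms alike. Drug therapies for COPD are recorded during the study, so departures can be described.

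Much of this stands, and it rules out several stronger readings that a reader might infer:

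- *That an inhaled-steroid user cannot possibly meet both rules.* The qualifier leaves room for a compatible reading. The text does not state it, however, and the guideline-treatment sentence carries no such qualifier.
- *That mucolytics and antitussives are guideline treatment withdrawn by the ban.* The document does not say what the guideline's basic treatment contains.
- *That the treatment comparison is biased.* No mechanism acting differently on blinded arms is shown.
- *That AECOPD duration becomes uninterpretable.* It becomes harder to interpret if care during episodes varies, but no more than that follows.

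The defence does not remove the core. The systemic-only reading is a guess, and the slip, if it is one, stands in the operative section and in the flow chart caption. Nor is this detail left to a fuller document: the rules are stated and they disagree.

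**Conclusion.** The point holds as a conflict between stated rules. It is firm for glucocorticoids, because the Background and the Exclusion criteria support it from within the document. It is weaker for mucolytics and antitussives. The exacerbation rule is plainly inconsistent between the Abstract on one side and the Intervention measures section and Fig. 1 caption on the other.

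The effect is on what counts as an event, how many events are recorded, whether the result can be read as the formula added to usual care, and patient safety. Blinding limits bias between arms, so the expected harm to the comparison is added variability and an ill-defined background rather than a shift in one direction.

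Its size cannot be stated as a number. The document does not give the share of patients on inhaled steroids at entry. Projecting earlier exacerbation rates would count all episodes, not those handled differently because of the wording. The conclusion assumes that sites work from text like that in the article; a full protocol with one clear rule would reduce the point to a correction of the article.

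**What to change.** The sponsor's clinical lead should reconcile the Abstract, the Fig. 1 caption, the Exclusion criteria and the Intervention measures section so that:

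- the prohibited-drug rule, including route, agrees with guideline basic treatment and with the instruction on prior treatment;
- one rule for treatment at an AECOPD appears in all places and covers both the 24-week treatment period and the follow-up.

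Which clinical rule applies is for the sponsor to decide; this review takes no view.

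On the statistical side, patients whose background drugs change, including those who take a prohibited drug, should stay in the intention-to-treat analysis. Adjustment for inhaled-steroid use at entry is optional, and only if that use is recorded at week 0. The article says COPD drugs are recorded during the study but does not list this item at baseline. Such a covariate would not in any case cure contradictory instructions.

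The cost is a clarification or amendment submitted to the ethics committee and a memo to sites. Recruitment began in November 2018, so the clarification should carry a date that identifies patients enrolled before and after it. Sample size and visit schedule do not change.

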### Outcome measures

#### Primary outcome measure

The frequency of AECOPD is the primary outcome measure. AECOPD is characterized by increased respiratory symptoms beyond daily routine variation and requires a change in regular medication. Its reduction is a major goal of COPD management and an important indicator for evaluating the treatments. AECOPD is considered if at least two major symptoms or one major symptom plus more than one minor symptoms occur: major symptoms are increased difficulty in breathing, increased sputum volume, purulent sputum; minor symptoms are upper respiratory tract infection, unexplained fever, and wheezing. If the interval between two onsets of acute exacerbation is less than 1 week and the acute exacerbation lasts for at least 2 days, it is counted as one acute exacerbation event. The frequency and duration of AECOPD occurrences during the 24-week treatment period and 7-month follow-up will be counted and the total number and average frequency and duration determined.

#### Secondary outcome measures

##### AECOPD

Time of first AECOPD occurence, the interval between two onsets of acute exacerbation, the duration of AECOPD, and the severity of AECOPD after the treatment.

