### Withdrawal, dropout, and discontinuation

Participants are free to withdraw at any time during the trial. Participants who wish to withdraw will be offered the option to cease trial medication but continue attending scheduled visits for outcome measurement. Participants who withdraw will be followed to investigate the reason for withdrawal. Participants may be advised to discontinue the treatment if there is a product-related adverse event of a serious nature or if the participant was not compliant with the study requirements. Discontinuers will not be replaced by new participants. Intention-to-treat analysis will be performed on missing data from discontinuers with the last observation carried forward method.

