### Sample size

A total of 100 patients will be enrolled in this study with 50 in each group. The frequency of AECOPD is the primary outcome. According to previous studies [15, 16], the exacerbation frequency increased 1.17 times each year when receiving conventional medicine, 0.97 times each year when receiving TCM, and 0.68 times each year when receiving both conventional medicine and TCM. Assume that promotional value is achieved only when the exacerbation frequency decreases at least once for each patient every 6 months. The standard deviation (SD) value is 1.25 times per year, the two-sided α is 0. 05, and β is 0. 10. Based on the formula:
$$ \left(\frac{2{\left({\mu}_{\alpha }+{\mu}_{\beta}\right)}^2{\sigma}^2}{\delta^2}\right) $$of the comparison between the means of the two samples, the sample size in each group is 40. Considering a 20% dropout rate over the course of the study, 50 patients will be enrolled in each group and the total sample size will be 100.

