### Statistical analysis

All data will be analyzed by an independent statistician using SAS 9.4. For all analyses, *P* < 0.05 is considered statistically significant. Measurement data will be presented as number of cases, mean, standard deviation, minimum, median, maximum, upper quartile (Ql), lower quartile (Q3), and 95% confidence interval (95% Cl) data. Paired-sample *t*-test or signed rank sum test will be used to compare the difference between the two groups or pretreatment and posttreatment within one group. Analysis of covariance will be used to compare the differences of center effector other confounding factors.

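### The between-group tests named in the article do not suit time to first AECOPD, duration or interval, which are censored or exist only for patients with enough events

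*Protocol article*

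**What the plan says.** Under the AECOPD heading of the secondary outcomes, the article lists "Time of first AECOPD occurence, the interval between two onsets of acute exacerbation, the duration of AECOPD", and then severity after the treatment. It does not say how a patient with no event, or with only one, enters these outcomes.

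Under Primary outcome measure, exacerbations over treatment and follow-up are to be counted and "the total number and average frequency and duration determined". An average is therefore planned for duration. No summary is stated for time to first event or for the interval.

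Statistical analysis covers all data in one short paragraph. Its group comparison is a paired t-test or "signed rank sum test will be used to compare the difference between the two groups or pretreatment and posttreatment within one group", with analysis of covariance for centre and confounding factors. No survival or recurrent-event method is named.

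The one missing-data rule, under Withdrawal, dropout, and discontinuation, is "Intention-to-treat analysis will be performed on missing data from discontinuers with the last observation carried forward method". It concerns discontinuers, not completers who had no exacerbation.

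**The concern.** The three outcomes differ in how they fail to give every patient a number:

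- Time to first AECOPD exists for everyone but is right-censored in patients who reach the end of observation without an event.
- Average duration per event exists only with at least one event.
- The interval between onsets exists only with at least two.

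A t-test or rank test on observed values uses only patients who have one. Whether a patient has one depends on exacerbation frequency, the primary outcome and the thing SHGBZK is expected to reduce. The patients compared are then selected by a post-randomisation event, and differently in each arm.

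For time to first event, the event-free patients, who carry the most favourable information, would drop out. Duration matters too: the Discussion part of the Abstract puts a reduction in both frequency and duration of exacerbations in the trial's hypothesis.

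**Working it through.** The article gives no figure for the share of patients without events, so there is none to reproduce.

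**Inputs (Sample size section).** Placebo proxy: "the exacerbation frequency increased 1.17 times each year when receiving conventional medicine". SHGBZK proxy: "0.68 times each year when receiving both conventional medicine and TCM". SD 1.25 per year. The rates are read as events per patient-year, although the text speaks of an increase. Observation is 24 + 28 = 52 weeks (Abstract). Constant rates and complete follow-up are assumed.

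**Model 1, Poisson, T = 1 year.** P(0) = exp(−μ); P(fewer than 2) = exp(−μ)(1 + μ).

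- μ = 1.17: P(0) = 0.310; P(fewer than 2) = 0.673.
- μ = 0.68: P(0) = 0.507; P(fewer than 2) = 0.851.

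**Model 2, negative binomial.** Variance = μ + aμ². Matching SD 1.25 at μ = 1.17 gives a = (1.5625 − 1.17)/1.3689 = 0.287. P(0) = (1 + aμ)^(−1/a); P(1) = μ(1 + aμ)^(−1/a − 1).

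- μ = 1.17: P(0) = 0.365; P(1) = 0.319; fewer than 2 = 0.684.
- μ = 0.68: P(0) = 0.537; P(1) = 0.306; fewer than 2 = 0.843.

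With the same a, the SD at 0.68 is about 0.90. Imposing SD 1.25 there as well raises P(0) to 0.647.

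| | Placebo | SHGBZK |
|---|---|---|
| No event, Poisson / neg. binomial | 31% / 36% | 51% / 54% |
| No interval, Poisson / neg. binomial | 67% / 68% | 85% / 84% |
| Two or more events, neg. binomial, of 40 | 0.316 × 40 ≈ 13 | 0.157 × 40 ≈ 6 |

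If the words after the treatment in the outcome list mean only the 28-week follow-up, the Poisson shares are 53% and 69% with no event, and 87% and 95% with fewer than two.

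**Time to first AECOPD.** S(t) is P(0) with μ replaced by μt. Restricted mean R = 52 × ∫S(t)dt over the year. Mean among patients with an event = (R − 52·S(1))/(1 − S(1)).

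| | Placebo | SHGBZK | Difference |
|---|---|---|---|
| Event-only mean, neg. binomial (weeks) | 20.5 | 22.6 | 2.1 |
| Restricted mean, all patients, neg. binomial | 32.0 | 38.4 | 6.4 |
| Event-only mean, Poisson | 21.0 | 23.1 | about 2 |
| Restricted mean, all patients, Poisson | 30.7 | 37.7 | about 7 |

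The event-only comparison therefore shows about a third of the difference visible in all patients (2.1/6.4 = 0.33).

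**Power, Poisson case, 50 per arm.** Hazard ratio 0.68/1.17 = 0.58. Expected first events: 50 × 0.690 + 50 × 0.493 ≈ 59. Log-rank: √(59.2/4) × |ln 0.581| − 1.96 ≈ 0.13, so power is about 55%. A t-test on event-only times, simulated 4,000 times with independent samples, has power of about 9%.

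**The case against.** The strongest reply is that this is an article, and that survival methods, censoring rules and conventions for patients without events normally sit in the analysis plan, which is not shown. The paragraph on tests is generic and tied to no endpoint. That stands against any claim that the methods are simply missing. It does not remove the point, because the article does name its group comparisons for the trial's data, and those named do not fit these outcomes.

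Several stronger readings are tempting and are not supported:

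- A reader might infer that event-free patients will be excluded. Nothing says so; exclusion is where the named tests lead if no rule is added.
- A reader might call time to first AECOPD undefined in event-free patients. It is censored, and a standard survival analysis keeps them.
- A reader might say that half of each arm is lost. The shares differ by arm and by outcome, as tabulated.
- A reader might conclude that duration is biased in a known direction. The documents do not show that. Under one assumed link (duration of 10 days times the square root of patient frailty, unaffected by the drug), event-only means are 10.4 and 10.6 days, a gap of 0.2 days. In that illustration total days fall from 12.9 to 7.5 per patient-year, but this is only the rate ratio (12.9 × 0.68/1.17 = 7.5), so it shows no bias.

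The rates are also open to challenge. They come from earlier studies, and entry requires at least two exacerbations or one hospitalisation for AECOPD in the past year. At an assumed placebo rate of 2 per year, only about 14% (Poisson) to 21% (negative binomial, a = 0.287) would be event-free and 53% (negative binomial) would have two or more events. The counts of 13 and 6 patients are therefore not robust.

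Finally, total AECOPD days answers a different question from duration per event and partly repeats the primary outcome. That is accepted and should be stated with the result.

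**Conclusion.** The point holds as a mismatch between the stated tests and three secondary outcomes. Followed literally, the plan leaves first-event times without a method for censoring, and it compares duration and interval in subsets formed after randomisation. The event-free and no-interval shares are substantial and unequal between arms at the cited rates. They would shrink if the high-risk entry criterion raises event rates.

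The consequence that can be shown is lost information on time to first AECOPD: roughly two thirds of the between-arm difference disappears, and power falls from about 55% to about 9% in the Poisson case. For duration and interval, the comparison loses the protection of randomisation, but the size and direction of any bias cannot be derived from the documents. The primary outcome is not affected by this point. It should be settled before unblinding.

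**What to change.** State in the analysis wording, before unblinding:

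- **Time to first AECOPD:** all randomised patients, Kaplan-Meier curves with a log-rank test or Cox regression, censored at last contact.
- **Duration:** total AECOPD days per patient-year, zero for event-free patients, compared in all randomised patients by an independent-samples method such as a Wilcoxon rank-sum test or a negative binomial model with a follow-up offset. Say in the report that this measure also reflects event frequency.
- **Duration per event, interval between onsets and severity:** descriptive only, with the number of contributing patients in each arm.

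The cost is wording and modest programming. AECOPD is already recorded every 4 weeks and its duration is already to be collected, so no new data are needed. The price is that the per-event comparisons lose their inferential status.
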